### Research Hypothesis

The study hypothesis is to investigate whether providing information about sustainable living encourages individuals to adopt more nutritious dietary habits and increase their levels of physical activity, as compared to receiving information solely centered around health-related recommendations for dietary intake and physical activity. The hypothesis will be tested among office workers to explore the workplace as an arena for health promotion.

### Primary Objective

The primary objectives are to examine the amount of change in the consumption of nutrients (fat, protein, carbohydrates, and fibers), more climate-friendly foods (increased intake of plant-based food and less dairy, red and processed meat, diet-related CO_2_e), more organic food, and increased practice of active transportation and related environmentally friendly behaviors. This will be evaluated by studying 1 variable at a time plus creating aggregated variables (the sums of all servings of fruits and vegetables expressed as servings per day), as well as creating a Sustainable Lifestyle Index, where each variable will be scored and summed to derive an overall score for each person [57], where higher scores indicate a more sustainable lifestyle. Finally, we will study the excretion of pesticide residues in urine as a validation of the consumption of organic food and explore if the excretion differs between the arms after the 8-week intervention.

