### Power Calculations and Randomization

Participants working in the targeted offices will be cluster-randomized based on the office’s geographic location by using a computer-generated random number generator in the statistical software R version 4.3.2 or later (Multimedia Appendix 5) [56]. Based on simulations derived from the pilot study CLEAR 2018 (unpublished data) using diet-related CO_2_e expressed as kg/day/person derived from Meal-Q, where we have an effect size of *η*^2^=0*.*11 for the interaction, a sample size of 40 observations in each arm at each assessment is indicated for 80% power. The estimated sample size was based on the interaction effect between control and intervention arms on CO_2_e in a linear mixed model maintaining a significance level of 5% from the CLEAR 2018 study. We assume a dropout rate of 10% to 15% after baseline assessment, and therefore, we will recruit 47 people to each arm, in order to have at least 40 at the end of the study. If the dropout rate in this study is less than 10%, no particular method will be used to account for attrition.

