### Strengths and Limitations

A strength of the study is the low dropout rate, indicating that the participants found the study engaging and motivating. However, the pilot phase of the intervention study is relatively small and targets office workers at progressive companies, of which most are well educated and interested in healthy behaviors. Thus, it potentially leaves limited room for improvement over the 8-week intervention. Also, we will collect data related to a large number of exposures that may introduce the risk of chance findings.

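### About 11 to 15 outcomes are called primary with none in the lead, although only diet-related CO2e was used to size the trial

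*Protocol article*

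**What the plan says.** Under Primary Objective, the article groups the following as primary: four nutrients (fat, protein, carbohydrates, fibre); climate-friendly eating (more plant-based food, less dairy, less red and processed meat, and diet-related CO2e); organic food; active transportation; and related environmentally friendly behaviours. On method it says: "This will be evaluated by studying 1 variable at a time plus creating aggregated variables". The aggregate given is fruit and vegetable servings. A summed Sustainable Lifestyle Index is added, and finally urinary pesticide residues, worded as a validation of organic food intake and an exploration of a difference between arms. No variable is singled out and no order is given.

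Under Power Calculations and Randomization, the simulations were done "using diet-related CO_2_e expressed as kg/day/person derived from Meal-Q", and "a sample size of 40 observations in each arm at each assessment is indicated for 80% power". The section also says: "The estimated sample size was based on the interaction effect between control and intervention arms". The variable meant there is CO2e, and the level is 5%. No other variable is powered, and no other significance level appears in the article.

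The Research Hypothesis asks whether information about sustainable living "encourages individuals to adopt more nutritious dietary habits and increase their levels of physical activity". CO2e is not mentioned there. In the Discussion, Principal Findings describes the possible primary finding in terms of food habits and physical activity, and brings in CO2e and pesticide excretion as additional expectations.

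Strengths and Limitations concedes that "we will collect data related to a large number of exposures that may introduce the risk of chance findings". The article describes no countermeasure.

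**The concern.** Three sections give three different answers to the question of which result decides the trial. The power calculation points to CO2e. The hypothesis points to nutritious diet and physical activity. The primary objectives point to a long list in which CO2e is one entry. Overall physical activity, which is half of the hypothesis, is represented in that list only by active transportation.

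With no lead variable, any significant result on the list could be reported as a primary finding. The 5% level quoted for the design then describes one comparison and not the primary claim of the trial. The 80% power likewise applies to one variable. For the others the article gives no basis for judging whether a null result is informative.

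**Working it through.** **Inputs from the article.** Level 5% (sidedness not stated), power 80%, 40 per arm at each assessment, η² = 0.11 for the interaction, 47 recruited per arm, dropout 10% to 15% (Power Calculations and Randomization). Three assessments: baseline, 4 and 8 weeks (Study Design and Sample Size). The variable list comes from Primary Objective.

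**1. The stated sample size.** f² = 0.11/(1 − 0.11) = 0.1236. With 80 participants the noncentrality is 0.1236 × 80 = 9.89. For the arm-by-time interaction over three assessments (2 numerator df), an F test at 5% has power 79.4% with 77 denominator df and 80.3% with 156. This reproduces the stated 80% at 40 per arm. A 1-df contrast would have 87.4% at the same size, so the stated number fits the 2-df interaction. For dropout, 47 × 0.85 = 39.95, in line with the aim of 40 at the end. The check uses individual-level df and ignores clustering. It shows only that the published size belongs to CO2e at 5%.

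**2. Counting the primary variables.**
- Individual variables: fat, protein, carbohydrates, fibre (4); plant-based food, dairy, red meat, processed meat, CO2e (5); organic food, active transportation, environmentally friendly behaviours (3). Total 12, or 11 if red and processed meat are one variable.
- Adding the fruit and vegetable aggregate and the Index: 14, or 13.
- Adding urinary pesticide residues: 15, or 14.

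The behaviours and the pesticide residues are plural, so the count could also exceed 15.

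**3. Chance of at least one false positive.** Assume every variable is tested at 5% and there is no true effect. Under independence this is 1 − 0.95^k. For the correlated case I used simulated equicorrelated normal statistics (400,000 draws, two-sided 5%). The correlations are assumptions; the article gives none.

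| Variables k | Independent | r = 0.3 | r = 0.5 | r = 0.7 |
|---|---|---|---|---|
| 11 | 43.1% | 37.4% | 30.3% | 22.2% |
| 12 | 46.0% | 39.7% | 32.0% | 23.1% |
| 13 | 48.7% | 41.8% | 33.5% | 24.1% |
| 14 | 51.2% | 43.8% | 35.0% | 24.9% |
| 15 | 53.7% | 45.7% | 36.0% | 25.5% |

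The expected number of false positives does not depend on correlation: 11 × 0.05 = 0.55 to 15 × 0.05 = 0.75.

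**4. Adjusting instead of ranking.** Bonferroni over 15 gives 0.05/15 = 0.0033 per test. Power for CO2e at 40 per arm then falls from about 80% to about 42% (77 df) or 45% (156 df). Bonferroni is conservative for correlated variables, so this only illustrates that ranking costs less than adjusting.

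**The case against.** A reader might infer that a false-positive primary result is more likely than not. The article does not support that. Passing one half needs at least 14 independent tests, and the narrower counts of 11 to 13 stay below it. Independence cannot hold in any case. The Index is a sum of scored variables, fruit and vegetable servings overlap plant-based food, and CO2e and the nutrients are all calculated from the same Meal-Q answers. At every correlation in the table the figure is below one half.

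Two further points stand. The 5% is stated only for the CO2e sample size, so applying it to each variable is an inference, although no other level is given. And a multiplicity procedure is commonly left to the analysis plan, which is not shown, so one cannot conclude that no error control exists anywhere.

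These points reduce the size of the problem but do not remove it. Which outcome is primary is stated in this article, and it is stated as a list. An adjustment method in another document would not tell the reader which outcome leads, nor remove the mismatch between the powered variable and the hypothesis. Admitting the risk of chance findings does not control it. The exploratory wording covers only the pesticide comparison, while the rest carries the primary label alongside a conventional power calculation.

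It can also be argued that making CO2e primary bends the scientific question to fit the power calculation. That is a fair objection, and it is why the hypothesis has to be reconciled openly with the choice.

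**Conclusion.** The point holds. The article gives primary status to about 11 to 15 variables without ranking them, sizes the trial on one of them, and states a hypothesis that does not name that one. If each is tested at 5%, the chance of at least one false-positive primary result is 43% to 54% under independence. It is more plausibly about 25% to 46% for 15 variables (22% to 37% for 11) at assumed correlations of 0.7 to 0.3. This rests on three assumptions: the 5% level applies to every variable, no true effect exists, and the correlations are roughly equal. The exact figure is uncertain, but over this range it stays at more than four times 5%.

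**What to change.** Designate diet-related CO2e as the single primary outcome at 5%, tested by the arm-by-time interaction on which the sample size rests. Reclassify the other variables under Primary Objective as secondary or exploratory, reported with estimates and confidence intervals and without confirmatory claims. If an ordered list of secondary outcomes is wanted, the investigators should choose it. Reconcile the Research Hypothesis and Principal Findings with this choice, so that the hypothesis, the powered variable and the expected main finding name the same outcome.

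**Cost.** The stated 40 and 47 per arm are unchanged. The other variables lose primary status, including the nutrition and activity measures that the hypothesis is about. The change is also more than rewording: Future Directions says that pilot data collection has ended and analysis is ongoing, and Results reports data from 33 participants against a target of 94. It therefore needs a dated amendment and a registry update, stating whether anyone involved in the choice had seen pilot results by arm. The case for CO2e is that the sample size already rests on it, from the separate CLEAR 2018 data.

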### Secondary Objectives

Secondary objectives cover the evaluation of the participants’ workshop attendance rate; own goal setting; monitoring of behavior change (goal importance, self-efficacy, outcome expectations, and goal fulfillment); and supporting factors and obstacles regarding manager, colleagues, facilitating researchers, and family to study if there are any differences between the intervention and control arms (Multimedia Appendix 6). Also, data from the Discovery Tool app will be used to study if participants in the 2 arms identified different facilitators and barriers in the built, social, and organizational environment. Moreover, we aim to study if the intervention group reported a greater level of change in opinions and behaviors when it comes to environmental and climate aspects of their lifestyle, as compared to the control arm.

## Results

Funding for this study was granted by the Knowledge foundation (KKS) in October 2020 and approved by the Swedish Ethical Review Authority in June 2021, with an amendment approved in September 2022. The start of the study and recruitment of research team members were delayed due to the ongoing COVID-19 pandemic in 2021. However, we started informing potential study participants about the study during the spring of 2022 and were able to start the recruitment of participants and data collection in August 2022 (iteration 1), and the second round of data collection (iteration 2) started in March 2023. Iterations 1 and 2 will be referred to as the pilot phase of the SOFIA study.

Groups of 5 to 15 participants were included in the intervention and control arms, respectively, during each iteration of the data collection, and the data collection will continue in the coming years. As of June 2024, a total of 37 participants have been recruited, of which 21 were included in the intervention arm and 16 in the control arm. The dropout after randomization was 2 in the intervention arm and 2 in the control arm, resulting in data from 19 participants in the intervention arm and 14 in the control arm, and a dropout rate of less than 10%. A majority of the participants are female (24/33, 73%) and are working in company B (22/33, 67%). The results of the pilot phase are expected to be published in 2024 or 2025.

## Discussion

### Principal Findings

This study aims to increase the understanding of the effectiveness of promoting a sustainable lifestyle to motivate behavioral change toward more nutritious food habits and increased physical activity, as compared to providing information based exclusively on health-related arguments in line with recommendations for food habits and physical activity. By targeting motivation, capabilities, and opportunities based on the behavioral change wheel model [58], we intend to increase the effect of the intervention in this specific context; moreover, it improves the understanding of behaviors in relation to the workplace environment [32]. A potential primary finding of this study would be that the intervention arm that received information about a sustainable lifestyle improved their food habits and physical activity level equally, or more, as compared to the control arm receiving information about health-related recommendations. Additionally, it is anticipated that the study will show that a shift to a sustainable lifestyle will lower diet-related CO_2_e emissions and reduce the excretion of urinary residuals of pesticides to a larger degree in the intervention arm than in the control arm.

A novel feature of this study is the use of the workplace as an arena for health promotion, and in particular office workers, a group known to be sedentary at work [59]. A substantial proportion of the adult population spends a significant amount of time at work each day, and the advantage of an office-based intervention is that many individuals can participate simultaneously at work [23,60]. Moreover, from the employee’s perspective, these types of interventions are convenient and easily accessible and allow employees to interact and support each other in their efforts to undertake behavior changes [61]. Full-time employees spend up to 60% of their waking hours at work [62] and typically return repeatedly to the same location, providing a significant opportunity to deliver health interventions. Recent review articles show that multicomponent workplace dietary interventions are effective but also an unutilized area to positively influence dietary intake and health outcomes among office workers [63]. However, the intervention needs to be tailored to the workplace and use behavioral and cognitive strategies to be successful [64,65]

In addition, we focus on the individual’s behavior change as well as features on an organizational level to facilitate or hinder a sustainable or healthy lifestyle at work. By implementing a citizen science methodology within the trial, the participants (citizen scientists) collect data using the app, the Discovery Tool; are involved in analyzing the data and formulating a list of actions; and contacts managers to bring about changes in their workplace.

### Comparison to Prior Work

We are not aware of any similar work, but a recent randomized controlled trial was conducted to assess the effects of an app-based intervention to improve the dietary intake of people with type 2 diabetes [66]. The intervention lasted for 12 weeks, with each week covering a new diet-related topic, with emphasis on the recommended intake of fruits, vegetables, legumes, and whole-grain products and reduction of red and processed meat. Although the primary aim was not to reduce diet-related greenhouse gas emissions, nor did the intervention study include information about carbon footprint, it was hypothesized that behavior changes toward more healthy food choices, would also result in lower emissions of CO_2_e expressed as kg/day/person. However, ad hoc analyses of CO_2_e did not show any differences between the intervention and the control arm.

### Strengths and Limitations

A strength of the study is the low dropout rate, indicating that the participants found the study engaging and motivating. However, the pilot phase of the intervention study is relatively small and targets office workers at progressive companies, of which most are well educated and interested in healthy behaviors. Thus, it potentially leaves limited room for improvement over the 8-week intervention. Also, we will collect data related to a large number of exposures that may introduce the risk of chance findings.

### Future Directions

As of the summer of 2024, the data collection of the pilot phase of the SOFIA study has ended, and the analysis of data is ongoing. A continuation of the recruitment process is planned for the coming years until the target number of participants is met. For now, this study protocol may serve as a framework to guide both scholarly research and the implementation of lifestyle interventions in office contexts. We anticipate that the company partners, where the SOFIA intervention was conducted, may implement aspects of the study to bring about change in their organizations. Additionally, future studies should include more diverse groups of employees, for example, from the public sector as well as blue-collar workers

### Conclusions

In conclusion, given the ongoing climate change, negative environmental effects, and the global epidemic of metabolic diseases, a sustainable lifestyle among office workers holds an important potential to counteract this trend. There is an urgent unmet need to test the impact of a sustainable lifestyle intervention on food intake, physical activity, and environmental and climate-friendly behaviors. Thus, this study protocol responds to a societal need, by covering behavior changes of importance for successful implementation of sustainable lifestyle habits in an office setting.

## Appendix

Multimedia Appendix 1 Themes for workshops 1-5 for the experimental and control arms.

Multimedia Appendix 2 Program theory.

Multimedia Appendix 3 Intervention functions.

Multimedia Appendix 4 Screenshot showing portion sizes of food in the web-based dietary questionnaire.

Multimedia Appendix 5 R-syntax for randomization.

Multimedia Appendix 6 Questionnaire for goal setting and monitoring of behavior change translated to English.

Multimedia Appendix 7 Approved grant proposal.

## Abbreviations

CO2e: CO2 equivalents
NCD: noncommunicable disease
NNR: Nordic Nutritional Recommendations
SOFCO: Concepts for the Sustainable Office of the Future
SOFIA: Sustainable Office Intervention
WHO: World Health Organization
